**Fig 2 Fig2:**
[figure not shown]
Flow chart of the study

**Fig 3 Fig3:**
[figure not shown]
The MASTERY^©^ trial design

#### Control: usual care group

Women allocated to the control group received the usual medical care provided by the antenatal clinics and/or their health professionals. This included their regular weekly to monthly antenatal visits depending on their trimester and other complications. If during follow up, it was apparent that their asthma control deteriorated since prior assessment (for example; using their reliever three or more times a week, needing to increase their preventer dose), the participant was advised by the research team to contact their health professionals. The control group was also given a summarised version of the “Asthma and Pregnancy” brochure from the NAC which explained about asthma in pregnancy including first aid and emergency assistance number to use for any concerns regarding their asthma.

### Outcome measures

The primary outcome measure was change in asthma control as measured by the Juniper Asthma Control Questionnaire (ACQ - 7) [26]. Secondary outcomes included changes in Juniper’s mini Asthma Quality of Life Questionnaire (mAQLQ) score [27], lung function (FEV_1_ and FEV_6_), self-reported exacerbations (symptoms requiring bronchodilators), asthma-related health visits, days off work/study related to asthma, and oral corticosteroid use. Lung function testing (pre-bronchodilator) was performed by trained research assistants using EasyOne™ Worldspirometer (ndd Medizintechnik AG, Zurich, Switzerland). Maternal and neonatal outcomes data collected are the gestational age of the baby at delivery, development of any antenatal complications such as gestational diabetes, hypertensive disorders of pregnancy, fetal growth restriction, antepartum hemorrhage, and delivery details. Neonatal outcomes collected at delivery include birth weight centile, birth length, head circumference, and Appearance Pulse Grimace Activity and Respiratory (APGAR) scores at 1 and 5 min after delivery. Birth weight centiles were calculated using www.gestation.net/grow-au.aspx, which adjusted for maternal characteristics including height, weight, ethnicity, parity and fetal gender.

### Data collection and follow-up

ACQ, mAQLQ scores, asthma-related health visits, asthma-related days off work/study, and oral corticosteroid use were collected at baseline, 3 months and 6 months from baseline to allow comparisons. Identical data collection forms were used for both groups. Maternal and neonatal outcomes data were collected shortly after delivery by reviewing medical records. The assessors responsible for collecting outcome data at three and six months were masked to the participant group allocation.

### Sample size

A sample size of 28 per arm is sufficient to detect the minimum clinically important difference in ACQ score of 0.5 or more between treatment groups using a standard deviation of 0.66 [10, 28, 29]. We estimate, conservatively, that by 3 months, there will be an improvement of at least 0.5 in the ACQ score in the intervention arm and that the control arm could exhibit a very small improvement or no improvement at all in the ACQ score. If these improvements are sustained at 6 months, then with 28 evaluable subjects in each arm, and assuming an independence model for measurement variation, and an intraclass correlation of 0.5 (equivalent to a within patient variance of 0.218 when the total variance is 0.66^2^ = 0.436), the F-test, conducted at the 5 % significance level will have at least 80 % power to detect a treatment by time interaction effect. If these conjectured improvements by month 3 are not durable and the scores return, on average, to their baseline levels at 6 months, then both the F-test for the interaction and the two-sided *t*-test comparing the two arms at month 3 at the 5 % level of significance will continue to have at least 80 % power. To allow for approximately 25 % attrition, the target sample size has been inflated from 28 per arm to 36 participants per arm. The study is, however, not powered to detect differences in the secondary outcomes.

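### Thirty-six per arm leaves 27 evaluable at 25% attrition, not the 28 on which the power statements rest; month-3 t-test power is then about 78–79.5%, while the primary F-test stays above 80%.

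*Protocol article*

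**What the plan says.** All of this is in the Sample size section of the protocol article.

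- The base number: "A sample size of 28 per arm is sufficient to detect the minimum clinically important difference in ACQ score of 0.5 or more", with the calculation made "using a standard deviation of 0.66".
- The repeated-measures assumptions: an "intraclass correlation of 0.5 (equivalent to a within patient variance of 0.218", out of a total variance of 0.436).
- The power claim for the interaction test, made "with 28 evaluable subjects in each arm": the F-test "conducted at the 5 % significance level will have at least 80 % power".
- The fallback scenario: if the month-3 gain has gone by month 6, the section repeats the 80% floor for the F-test and extends it to a two-sided 5% t-test "comparing the two arms at month 3".
- The inflation, for attrition put at approximately 25%: "the target sample size has been inflated from 28 per arm to 36 participants per arm".

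The Data analysis section makes a REML mixed model with a treatment-by-time interaction the primary analysis and uses all observed data. The Trial status section reports that recruitment and follow-up are complete.

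**The concern.** The power statements are conditional on 28 evaluable women per arm, and the inflation is meant to secure that number after dropout. At the attrition rate the section itself gives, it does not: one woman per arm is missing. The month-3 t-test was sized with almost no margin, so losing even one per arm takes it below the stated floor.

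What is at stake is the accuracy of two stated figures: the attrition allowance and the month-3 power. The month-3 figure has some importance because the t-test is offered as reassurance for the case where the benefit does not last, and the Background names three months as one of the two times at which better control is hypothesised.

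**Working it through.** **Inputs (Sample size section).** Difference 0.5; SD 0.66; two-sided 5%; intraclass correlation 0.5 with within-patient variance 0.218; 28 evaluable and 36 randomised per arm; attrition approximately 25%. Allocation is 1:1 (Group allocation section).

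**1. Reproducing the 28.** The normal-approximation formula is n = 2(z₀.₉₇₅ + z₀.₈₀)² × SD² / difference². This gives 2 × (1.960 + 0.842)² × 0.4356 / 0.25 ≈ 27.4, rounded up to **28 per arm**. The plan's number is reproduced.

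It makes no difference whether 0.66 is read as the SD of a single score or of a change score. Under the stated variance components the change-score SD is √(2 × 0.218) = 0.660.

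**2. The attrition step.**

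- Left after 25% loss: 36 × 0.75 = **27** per arm.
- Needed to keep 28: 28 / 0.75 = 37.3, so **38** per arm (76 in total, against 72).
- Loss that 36 can absorb while keeping 28: 1 − 28/36 = **22.2%**.
- The common shortcut 28 × 1.25 gives 35, so it does not yield 36 either.

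**3. Month-3 t-test power.** The noncentrality is 0.5 / (0.66 × √(2/n)), which is 2.835 at n = 28 and 2.784 at n = 27. Three ways of turning it into power were compared:

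| Evaluable per arm | Exact two-sample t, df = 2n − 2 | Contrast with repeated-measures df = 2(2n − 2) | Normal approximation |
|---|---|---|---|
| 27 | 78.0% | 78.7% | 79.5% |
| 28 | 79.5% | 80.2% | 80.9% |

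The middle column uses the variance 2 × 0.218 for the change, with 104 and 108 degrees of freedom. At 27 all three methods fall below 80%. At 28 only the exact two-sample t does, by half a percentage point. By the exact t, 29 per arm is the smallest number that reaches 80% (80.9%).

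**4. Primary interaction F-test.** Assume three time points, compound symmetry, complete data and no change in the control arm. Let c be the between-arm differences over time, centred on their mean. The noncentrality is λ = (n/2) × Σc² / 0.218, with 2 and 2(2n − 2) degrees of freedom.

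- Sustained pattern (0, 0.5, 0.5): c = (−1/3, 1/6, 1/6), so Σc² = 1/6.
- Non-durable pattern (0, 0.5, 0): c = (−1/6, 1/3, −1/6), so Σc² = 1/6 again. Power is the same in both scenarios.

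| Evaluable per arm | λ | Power |
|---|---|---|
| 26 | 9.94 | 80.0% |
| 27 | 10.32 | 81.7% |
| 28 | 10.70 | 83.1% |

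The F-test needs 26 per arm. Allowing for 25% loss, 26 / 0.75 = 34.7, so 35 per arm would do, and 36 covers it.

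**The case against.** The strongest reply has four parts.

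- **The attrition figure is hedged.** The section says approximately 25%, and 22% is not far off. That is fair as to size. It does not make 36 the right inflation for the rate named, and no standard formula turns 28 and 25% into 36.
- **The power claim is conditional on 28, and at 28 it is defensible.** This stands. A reader might infer that the month-3 t-test falls short of 80% at 28 as well as at 27. The document does not support that as a firm statement. It does not say how power was computed, the normal formula that yields 28 gives 80.9%, and a contrast using the repeated-measures degrees of freedom gives 80.2%. Only the exact two-sample t gives 79.5%.
- **Twenty-seven is not necessarily the month-3 number.** This also stands. The section does not say when attrition occurs. Women lost after month 3 would still provide month-3 data, and the mixed model uses all observed data. The figures at 27 therefore apply to complete cases with the full 25% lost.
- **The primary test is protected.** This stands too. A reader might infer that the trial is underpowered. On the plan's own assumptions it is not: the interaction F-test exceeds 80% at both 27 and 28, in both scenarios.

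**Conclusion.** The Sample size section is wrong as written on the attrition allowance. At 25% loss, 36 per arm yields one evaluable woman per arm fewer than the 28 that the power statements assume, and it is two randomised per arm short of the 38 needed.

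As a consequence, the 80% floor for the month-3 t-test is missed by about 0.5 to 2 percentage points at 27 per arm, whichever method is used. At 28 the claim is borderline and cannot be called wrong without knowing how it was calculated.

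These figures rest on the plan's own difference, SD and variance components, and on counting only women with complete data. The F-test figures also assume compound symmetry.

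Severity is minor. The primary analysis keeps its stated power, and no conclusion about the validity of the trial follows.

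**What to change.** Reword the end of the Sample size section, with no added enrolment:

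1. State that 36 per arm allows about 22% attrition if 28 are to remain evaluable, or that 25% attrition leaves 27.
2. State the month-3 t-test power as about 78% at 27 per arm and just under 80% at 28 by the exact t. Name the method, since the normal approximation gives 79.5% and 80.9%.
3. Add that the treatment-by-time F-test, the primary test, has about 82% power at 27 and 83% at 28.

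The cost is a sentence or two and a slightly less favourable month-3 figure. Neither the analysis nor the conduct of the trial changes. As recruitment and follow-up are complete, the results report could give the restated figures.

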### Data analysis

All analyses will be performed using SAS version 9.4 (SAS Institute, Cary, NC, USA) and SPSS version 19.0 (IBM SPSS Statistics for Windows, Armonk, NY). The baseline characteristics of the two groups will be compared using Student’s *t*-test for normally distributed continuous variables, Mann-Whitney ‘U’ test for non-normally distributed continuous variables and chi-square or Fisher’s exact test as appropriate for categorical variables. The primary analysis will be performed according to the intention to treat (ITT) principle on the “full analysis set”.

Primary inferential analyses will be conducted using a mixed effects model for the ITT population. This model will include treatment group and time as fixed effects with an interaction between treatment and time to ascertain if the groups behave differently over time. All observed data will be included in the analysis, with the mixed-effects models, fitted by residual maximum likelihood (REML) assuming non-informative dropout such that the probability of dropout may depend on a participant’s previous response but not on current or future responses. In supportive analyses, changes in the primary outcome from baseline to 3 and 6 months will be compared between groups using linear regression modelling adjusting for baseline scores. Baseline demographic and clinical factors that appear to be different will be included as potential covariates in all regression models.

We will also compare the proportion of participants whose ACQ score improves more than 0.5 (MCID) over the study period, the proportion in whom asthma remained “not well controlled’ (ACQ score 1.5 or greater) and those whose asthma was “well controlled” (ACQ score less than 1.5) at each time point [26]. Secondary outcomes will be summarised using descriptive statistics and analyses will be performed using the methods described above.

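### The primary mixed model uses baseline ACQ only by differencing, which is valid but less efficient than the baseline adjustment the plan leaves to a supportive analysis

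*Protocol article*

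**What the plan says.** In the protocol article, the Data analysis section defines the primary inferential model as a mixed-effects model fitted by REML to all observed data: "This model will include treatment group and time as fixed effects with an interaction between treatment and time". Baseline ACQ is not listed as a covariate, and nothing says that the two arms share a baseline mean.

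Adjustment for baseline comes in the supportive analyses, where changes to 3 and 6 months are "compared between groups using linear regression modelling adjusting for baseline scores". Other baseline factors may enter the regression models if they look different between arms.

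The Sample size section uses a "minimum clinically important difference in ACQ score of 0.5 or more between treatment groups using a standard deviation of 0.66", "assuming an independence model for measurement variation, and an intraclass correlation of 0.5". On that basis it states that "the F-test, conducted at the 5 % significance level will have at least 80 % power to detect a treatment by time interaction effect" if the month-3 gain is sustained at month 6. If scores return to baseline by month 6, it says that this F-test and a two-sided t-test "comparing the two arms at month 3 at the 5 % level of significance" "will continue to have at least 80 % power".

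**The concern.** The article does not say outright whether baseline ACQ is a response in the primary model, but the Sample size section settles it. With months 3 and 6 as the only responses, a sustained effect gives the same treatment difference at both visits, so the treatment-by-time interaction is zero and the F-test has no power beyond its 5% level. The claim of at least 80% power for a sustained effect therefore requires baseline as a third time level.

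In that model, with arm means free at baseline, the interaction contrasts are differences between arms in mean change from baseline. Baseline is accounted for by subtracting it in full, that is, with a slope of 1. At a correlation of 0.5 the best slope is 0.5. Two consequences follow:

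- The estimate carries more variance than it needs to. Randomisation makes the expected baseline means equal, and the model does not use this.
- A chance baseline difference is over-corrected, so the primary and supportive results can diverge for that reason alone.

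At stake is power and stability in a trial planned around 28 evaluable women per arm, when baseline ACQ is collected anyway.

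**Working it through.** **Inputs, all from the Sample size section.** SD 0.66, so total variance σ² = 0.66² = 0.4356; intraclass correlation ρ = 0.5; difference d = 0.5; n = 28 per arm; two-sided 5%. Scores at 0, 3 and 6 months are taken to have equal variances and equal correlations, as the stated model implies.

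**1. The plan's own figures.**
- Sample size: n = 2(1.960 + 0.842)² × 0.4356 / 0.25 = 27.4, so 28 per arm, as stated.
- Month-3 t-test: 80.9% power by the normal approximation, 79.5% by the noncentral t with 54 df.
- Interaction F-test with baseline as a response. The changes to months 3 and 6 have covariance σ²(1−ρ) × [[2,1],[1,2]] = 0.2178 × [[2,1],[1,2]]. The noncentrality is λ = (n/2) δ′C⁻¹δ.
  - Sustained, δ = (0.5, 0.5): 14 × 0.25 × 2 / (3 × 0.2178) = 10.71.
  - Non-durable, δ = (0.5, 0): the same expression, 10.71.
  - Power with 2 and 108 df is 83.2% in both cases (82.1% with 54 denominator df).

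The stated power is therefore reproduced, to within half a point for the t-test.

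**2. Variance with and without baseline adjustment.**
- Single visit, change: 2(1−ρ)σ² = 0.436. Adjusted: (1−ρ²)σ² = 0.75 × 0.4356 = 0.327. The loss is 1 − 0.327/0.436 = 25%. Power goes from 79.5% to 89.5%; equivalently, about 21 per arm would do in place of 28.
- Mean of months 3 and 6, change: [(1+ρ)/2 + 1 − 2ρ]σ² = 0.75σ² = 0.327. Adjusted: [(1+ρ)/2 − ρ²]σ² = 0.50σ² = 0.218. The loss is 33%. Power goes from 89.5% to 97.6%.

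**3. The 2-df test.** Given baseline, months 3 and 6 have covariance σ² × [[0.75, 0.25],[0.25, 0.75]] = 0.1089 × [[3,1],[1,3]].
- Sustained: λ = 14 × 0.25 × 4 / (8 × 0.1089) = 16.07. Information lost by the planned model: 1 − 10.71/16.07 = 33%. Power 83.2% to 95.2%.
- Non-durable: λ = 14 × 0.25 × 3 / (8 × 0.1089) = 12.05. Information lost: 1 − 10.71/12.05 = 11%. Power 83.2% to 87.5%.

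**4. Other correlations (assumed values, SD held at 0.66).**

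| ρ | Loss, single visit | Loss, mean of visits | 2-df power, sustained | 2-df power, non-durable |
|---|---|---|---|---|
| 0.3 | 35% | 47% | 68% to 93% | 68% to 77% |
| 0.5 | 25% | 33% | 83% to 95% | 83% to 88% |
| 0.6 | 20% | 27% | 91% to 97% | 91% to 93% |
| 0.7 | 15% | 20% | 97% to 99% | 97% to 98% |
| 0.8 | 10% | 13% | 99.7% to 99.9% | 99.7% to 99.8% |

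**5. Chance imbalance.** The standard error of the baseline difference is 0.66 × √(2/28) = 0.18 ACQ points. The change-based and adjusted estimates differ by (1 − 0.5) times the observed imbalance, so one standard error shifts one against the other by 0.5 × 0.18 = 0.09, roughly a fifth of the 0.5 target.

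**The case against.** The strongest reply is that nothing here is wrong. Comparing changes from baseline is unbiased under randomisation and holds its type I error. The planned F-test reaches 83% in both scenarios the plan names, and the month-3 test is at about 80%. An unconstrained longitudinal model is a recognised choice, and a baseline-adjusted comparison is also prespecified. Stratifying allocation by asthma severity should limit ACQ imbalance, though not remove it. All of this stands, and it makes the point one of efficiency.

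A reader might infer more than the documents support:

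- **That the primary analysis ignores baseline.** It does not; the interaction uses baseline by differencing.
- **That 25–33% of precision is lost whatever happens.** Those figures need ρ = 0.5 and the particular contrasts above. For the planned test in the plan's own non-durable scenario, the loss is 11%.
- **That the trial is underpowered.** The planned F-test does fall to 70.7% (84.4% with adjustment) if half the effect is lost by month 6, but that profile is an assumption from outside the plan, which makes no power claim for it.
- **That the supportive regression drops women with missing visits.** The article does not say how that regression treats missing scores.

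The rule about factors that look different does not answer the point either. It depends on the observed imbalance, and the gain from adjustment is there even when the arms happen to be balanced.

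**Conclusion.** The point holds as an efficiency recommendation. The primary model is valid and meets its stated power approximately, but it makes poorer use of baseline ACQ than a baseline-adjusted model would, and it is more sensitive to chance imbalance. At the plan's inputs, the planned 2-df test loses between 11% (non-durable) and 33% (sustained) of the available information, and single-visit estimates carry an avoidable 25% of variance. These sizes rest on the planning correlation of 0.5, equal variances and correlations across visits, and complete data on 28 women per arm. Under that covariance model the adjusted analysis is the more efficient at any correlation below 1, but the gain becomes small as the correlation rises. That baseline is a response level is inferred from the power statement, so the article should say so explicitly.

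**What to change.** Use one of two forms of the primary REML model:

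1. Keep baseline, month 3 and month 6 as responses, and constrain the arm means to be equal at baseline.
2. Take months 3 and 6 as responses, with baseline ACQ and baseline-by-time as covariates.

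In either form, name as the primary test the joint 2-df test that the treatment differences at months 3 and 6 are both zero, and report the adjusted difference with its confidence interval at each visit. Under the second form, do not carry over the treatment-by-time interaction as the primary test: with only those two visits it has zero noncentrality for a sustained effect. The separate regression can stay as a check.

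No new data are needed, since baseline ACQ is already collected. The cost is a revised model statement, a restated primary hypothesis and a matter of timing. The Trial status section reports follow-up complete and analysis in progress, so the change should be dated, justified and documented before any group comparison is seen. If that is no longer possible, keep the planned model as primary and report the adjusted model beside it, labelled as added later.

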### Ethical aspects

The study has been approved by the human research ethics committees of Monash University, Mercy Hospital for Women and The Royal Women’s Hospital. All participants provide written informed consent at the time of enrolment. The study has been registered with the Australian New Zealand Clinical Trials Registry: ACTRN12613000800729.

## Discussion

Innovative solutions are needed to support self-management and to improve asthma control during pregnancy. The MASTERY trial is designed to evaluate a telehealth program aimed at helping pregnant women with asthma to monitor their lung function and better manage their asthma during pregnancy. The Vitalograph COPD-6® is designed to enable the lung function data to be transmitted automatically via a Bluetooth connection to another enabled device (e.g. phone, computer). In our study, the Breathe-easy^©^ application installed on a smart phone acquires the data and transmits via internet to a secure website, which can be accessed only by patients and other authorized personnel.

Automatic transmission can minimise the risk of errors when data are entered/reported manually. The *Breathe-easy*^©^ application has been developed to record lung function data, asthma symptoms and medication usage and provides a user-friendly interface through a smart mobile phone. Recording symptoms as part of asthma management is known to reduce costs associated with unplanned hospitalisation and improved quality of life in asthma patients [13, 27, 28].

Daily recording of lung function and weekly assessment of asthma symptoms could allow women to recognize early worsening of their asthma control. Participants in the intervention group were provided with a WAAP as it was part of the algorithm of the telehealth intervention (MASTERY). The automated messages sent to each participant in the intervention group contained feedback regarding their asthma control/condition and asked them to refer to their individualised WAAP for further management. The individualised WAAP designed for each woman provided clear guidelines in terms of actions to be taken in case of worsening asthma. Although the WAAP alone may be effective in achieving asthma control, the telehealth (Breathe-easy^©^) app had additional features for monitoring and recording symptoms and lung function to give instant feedback to participants about their asthma status using an algorithm based on an individualized WAAP.

The proposed intervention has the potential to identify worsening asthma control early and prevent asthma exacerbations during pregnancy by regularly monitoring lung function and asthma symptoms. This may translated to reduce health care costs through fewer asthma-related unplanned medical and emergency department visits. If the intervention is efficacious, this could potentially influence clinical practice and health policy. The *Breathe-easy*^©^ application could be made widely applicable for routine clinical use, particularly for those with chronic respiratory conditions.

